### Study design

2.1

We use two treatment arms in a longitudinal randomized single‐blinded (rater)controlled parallel group design with points of measurement at Day 1–3 after hospital admission (baseline, T0), after 4 weeks (T1a), at discharge (T1b), and 6 months after hospital admission (follow‐up, T2; see Figure 1).

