#### PA—Objective

2.7.1

To objectively measure steps and overall PA we use ActiGraph GT1M accelerometers (ActiGraph). The GT1M counts the incidences of change in acceleration per minute and can therefore measure the amount of PA. Additionally, it measures steps. Accelerometers have already been used in former research and proved being a reliable instrument for measuring PA (Kaminsky & Ozemek, 2012; Silva, Mota, Esliger, & Welk, 2010), also for samples with patients with mental disorders (Petzold et al., 2017). For different activity levels, we set thresholds according to the ActiLife Software (ActiLife 6 User's Manual, 2008): light (≤1952 counts per minute), moderate (1953–5724 counts per minute), hard (5725–9498 counts per minute), and very hard (≥9499 counts per minute). For measuring the activity of less active people, two to three valid days of wearing the accelerometer are enough for sufficiently valid data (Kocherginsky, Huisingh‐Scheetz, Dale, Lauderdale, & Waite, 2017). Therefore, patients are instructed to carry the accelerometer around their hip for 3 consecutive days while being awake. Mean step count is used as summary measure format.

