#### Calculation of power and sample size

2.9.1

*For depressive symptoms,* Cooney et al. (2013) report a large effect size of −1.22 (−2.21, −0.23) in favor for exercise plus treatment versus treatment, and a medium effect size for all control conditions with *d* = −0.62. For the subgroup of light/moderate activity interventions, they report an also large effect size of −0.83 (−1.32, −0.34). Therefore, we also expect a medium effect size in the MADRS between both groups at discharge. *For PA,* Heinzel et al. (2015) find an effect size of *d* = −0.49 (95% CI −0.91 to −0.06, *Z* = 2.23, *p* = 0.03) in favor of exercise for body functioning/fitness indicators in five trials of their meta‐analysis. Thus, we expect a small but close to moderate effect size for PA difference at discharge.

Taken together, we assume a small to moderate effect size for the group difference. According to Cohen (1988), *f*
^2^ = 0.02 and *f*
^2^ = 0.15 represent small and moderate effect sizes, respectively. Conservatively, we aim to detect a small effect of *f*
^2^ = 0.06. For this, in a parallel group, fixed sample trial with a multivariate analysis of variance (MANOVA; 5% significance level with a power of 95%) a sample size of 262 is necessary (using G*Power Version 3.2.1). F. B. Schuch et al. (2016) find a dropout rate of 17.2% in their meta‐analysis for depressed patients in exercise studies. Assuming a possible additional loss of 17% through overall missing data that is seen in studies using accelerometers (Helgadóttir et al., 2017), the sample size is enlarged to be 396, for practical reasons rounded up to 400 (40 per participating center, enables 34% of data loss by dropout or missing data).

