#### Statistical analyses

2.9.2

Accelerometer data are analyzed using Actigraph Software ActiLife 6.13.3. Minimal wearing time is eight hours a day, a PA measure of two complete days serving as minimal criteria to count as valid measurement.

Demographic and clinical characteristics of the study population are reported using descriptive statistics. Differences in baseline values between groups are assessed with chi‐squared tests or Fisher's exact test for nominal data and two‐sample *t*‐tests or Mann–Whitney *U* test for metric/ordinal data scales. Missing data will be imputed by multiple imputation techniques.

For assessing group differences in the primary outcome variables depression and PA, MANOVA is done with IBM SPSS Statistics. If baseline group differences occur (e.g., for age, gender, PA baseline level, comorbidity), we adjust for by analysis of covariance (MANCOVA). Furthermore, we report the percentage of participants in each group meeting criteria of WHO‐recommended PA to provide a benchmark to other PA studies. Likewise, we present remission and response rates for PI and TAU, respectively. Additional subgroup analyses are executed if necessary (e.g., concerning trial site, season of data collection, and medication). If MANOVA shows significant results, single ANOVA and discriminant analysis are executed to investigate the relationship between and the influences on the dependent variables.

Secondary data are analyzed by methods appropriate for the respective scale of the parameter and suitable for specific research questions. Results here are of exploratory nature.

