### Trial status and dissemination

3.1

Recruitment started in August 2016 and finished at the end of January 2020. Results are published, independently of magnitude or direction of found effects. Primary outcome paper is published first. Following additional dissemination via conference presentations and media is envisaged, likewise.

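### Season is planned as an optional split by date of data collection; a prespecified season-of-admission covariate for steps would gain some precision at almost no cost

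*Protocol article*

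**What the plan says.** The protocol article mentions season once, in Statistical analyses (2.9.2): "Additional subgroup analyses are executed if necessary (e.g., concerning trial site, season of data collection, and medication"). It is an example of an additional analysis, done at discretion and defined by when the data are collected.

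The same section sets the primary analysis: "For assessing group differences in the primary outcome variables depression and PA, MANOVA is done with IBM SPSS Statistics". Its covariate rule is conditional: "If baseline group differences occur (e.g., for age, gender, PA baseline level, comorbidity), we adjust for by analysis of covariance (MANCOVA"). Season is not among the examples, although the list is open. Randomization (2.4.1) stratifies by center only.

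For the step outcome, PA—Objective (2.7.1) says: "Mean step count is used as summary measure format". Study design (2.1) places the visits at baseline, 4 weeks (T1a), discharge (T1b) "and 6 months after hospital admission (follow‐up, T2; see Figure 1"). Research hypotheses (1.5.3) lists a shorter hospital stay among the expected effects of the pedometer intervention. On calendar coverage, Trial status and dissemination (3.1) states: "Recruitment started in August 2016 and finished at the end of January 2020". Every season is therefore represented.

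**The concern.** The plan recognises season as relevant but handles it with the wrong tool, the wrong variable and an open trigger.

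- **Tool.** A subgroup analysis asks whether the treatment effect differs by season. It takes no seasonal variance out of the overall arm comparison. If season moves steps in both arms, that variation stays in the error term unless a baseline imbalance happens to bring season into the MANCOVA.
- **Variable.** The date of the T1b measurement depends on length of stay, which the trial expects the intervention to change. Grouping patients by season of data collection at T1b therefore conditions on something treatment may affect. Season of admission is known before allocation, and it fixes the calendar timing of T1a and T2.
- **Trigger.** No criterion says when the split becomes necessary, so the decision can be taken after results are seen.

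At stake is some precision on the step outcome, and the chance that differences between small season groups are over-read.

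**Working it through.** **1. The plan's own sample size.** Inputs from Calculation of power and sample size (2.9.1): "5% significance level with a power of 95"%, and "Conservatively, we aim to detect a small effect of" f² = 0.06. For a MANOVA with p = 2 outcomes and k = 2 groups, power comes from the noncentral F with df1 = p(k−1) = 2, df2 = N−k−p+1 and λ = N·f². At N = 262: df2 = 259, λ = 262 × 0.06 = 15.72, power 0.951. The smallest N reaching 95% is 261, or 262 with equal arms. Inflation: 262/(1−0.34) = 397, against the stated 396. The plan's figures reproduce.

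**2. Cost of a season term.** Taking 3 degrees of freedom from df2 (259 to 256), with season explaining nothing, leaves power at 0.951.

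**3. Gain without baseline steps in the model.** The documents give neither a seasonal amplitude nor an SD of steps. Assume a sinusoid of amplitude A (half the peak-to-trough difference), admissions spread over the year, and a total SD of 3000. Then R² = A²/(2·SD²), and the gain in effective sample size is 1/(1−R²) − 1.

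| A (steps) | R² | Gain |
|---|---|---|
| 500 | 250,000/18,000,000 = 0.014 | 1.4% |
| 750 | 562,500/18,000,000 = 0.031 | 3.2% |
| 1000 | 1,000,000/18,000,000 = 0.056 | 5.9% |

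On the planned MANOVA, assume season acts on steps but not on MADRS, equal standardised effects, and uncorrelated outcomes. For R² of 0.01, 0.05 and 0.10 the required N falls from 261 to 260, 254 and 247, and power at 262 rises from 0.951 to 0.952, 0.956 and 0.961.

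**4. Gain with baseline steps in the model.** Let s be the seasonal share of variance (R² above), the same at both visits, and r the season-free correlation between baseline and follow-up steps (assumed 0.3 to 0.7). Let c be the correlation of the two seasonal components: c = −1 at six months, and c = cos(2π·28/365.25) = 0.886 at four weeks. Residual variance, as a share of the total, is 1 − (r(1−s) + c·s)² without season and (1−s)(1−r²) with it. The gain is the ratio minus 1.

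- T2, A = 500, r = 0.3: 0.9205/0.8974, gain 2.6%. With r = 0.7: 0.5425/0.5029, gain 7.9%.
- T2, A = 1000, r = 0.3: 0.9481/0.8594, gain 10%. With r = 0.7: 0.6333/0.4817, gain 31%.
- T1a, r = 0.3 to 0.7: gain 0.7% to 0.9% at A = 500, and 2.8% to 3.5% at A = 1000.

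Baseline steps thus absorb part of the season at four weeks. At T2 the reversed cycle weakens the baseline correlation, and the season term restores it.

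**5. What a split can show.** The plan allows 34% loss, leaving 400 × 0.66 = 264 evaluable. Assume four equal seasons of about 66 patients. A two-sample t-test at d = 0.49, the fitness effect the protocol cites, has power 0.50 with 33 per arm, against 0.98 with 132 per arm. The MANOVA at f² = 0.06 has power 0.39 within one season (n = 65).

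**The case against.** The strongest reply is that nothing here is an error. Season is one example in one sentence of a condensed article, the sample size is sound, and the gain is small in a trial planned at 95% power. For steps alone at d = 0.49 with 264 evaluable, power goes from 0.978 only to 0.983 at R² = 0.05. The amplitude and SD are assumed. Four season categories would capture only about 81% of a sinusoid's variance, (sin(π/4)/(π/4))². The protocol does not offer subgroups as noise reduction, does not fix four seasons, and powers its comparison at discharge rather than at T2. All of this stands and limits the size of the point. It does not make a discretionary split by a post-randomisation date a good way to handle a factor the plan itself names.

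Stronger readings should be resisted:

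- A reader might infer that the six-month shift confounds the treatment effect at T2. It does not: T2 is set by the admission date and allocation is 1:1 within center, so the shift is equal in expectation in both arms and drops out of their contrast. It adds noise to individual change only.
- A reader might infer that season can enter only as a subgroup. The open MANCOVA list could admit it, but only after an imbalance is seen.
- A reader might take the steps to be outdoor steps. The protocol counts all waking steps, many of them during an inpatient stay, where any seasonal swing may be weaker.
- The post-randomisation point applies to T1b only, and the documents do not show how many patients would change season because of treatment.

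**Conclusion.** A minor but valid precision point. The planned split by season of data collection does nothing for the arm comparison, rests on a post-randomisation variable at T1b, and has no stated trigger. There is no bias in the primary comparison, and the 262 is not affected. Under an assumed swing of ±500 to ±1000 steps and an SD of 3000, the loss is worth about 1.4% to 5.9% of patients for the step outcome. It is less at four weeks if baseline steps are in the model, and 2.6% to 31% at T2 if they are, over assumed correlations of 0.3 to 0.7 and an equal swing at both visits. A weaker swing on the ward would shrink these figures.

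**What to change.** Replace the season subgroup with one sentence: the step outcome is adjusted at every visit for season of the admission date, preferably as sine and cosine terms (2 degrees of freedom), otherwise as four categories (3 degrees of freedom). If effect modification by season is of interest, test a single arm-by-season-of-admission interaction, labelled exploratory, and do not split by season of data collection.

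The cost is that sentence and 2 to 3 degrees of freedom. The admission date already sets the visit schedule, so no new data, visits or patients are needed. Recruitment has closed, so the choice should be fixed before any unblinded analysis.

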### Study approvals

2.10

The Ethics Commission of Charité Universitätsmedizin Berlin, Germany approves this trial (EA1/088/16). It also is registered (ClinicalTrials.gov Identifier: NCT02850341, registered January 08, 2016). Three amendments were further approved: (1) the extension of the local to a multicenter trial (May 2016), (2) an additional measurement of hand grip strength (May 2017), and (3) the addition of a reimbursement for the participation in the follow‐up‐measurement (June 2017).

## RESULTS

3

### Trial status and dissemination

3.1

Recruitment started in August 2016 and finished at the end of January 2020. Results are published, independently of magnitude or direction of found effects. Primary outcome paper is published first. Following additional dissemination via conference presentations and media is envisaged, likewise.

## DISCUSSION

4

Our study is designed to test the efficacy of an adjunct PI in inpatient TAU. Since now, there is only little evidence available about flexible walking interventions in inpatient care for depressed patients. Hence, studies show promising results that this type of intervention might be well accepted especially by depressed patients (Busch et al., 2016) and effective in the reduction of symptoms.

Among the methodological constraints of this study are the absence of a nontreatment control group. However, we already have good evidence for the efficacy of inpatient depression treatment (Cuijpers et al., 2011; Mass, Backhaus, Hestermann, Balzer, & Szelies, 2019) and it would be unethical to deny treatment for severely depressed persons for such purposes. Furthermore, we cannot rule out the possibility that the mere act of measuring PA with accelerometers may have an influence on the participants' PA and PA motivation in both groups. We will bear this in mind when analyzing and interpreting our results. Another weak point may be that TAU already comprises PA interventions so that our effect to be found is exclusively due to the PI intervention, not to the efficacy of PA, overall. Yet, the use of an individually applicable add‐on intervention is the most suitable for a broad distribution in psychiatric clinics. It could be very easily adopted and implemented in routine inpatient treatment with the option of being continued even afterward. Physical exercise is effective in the treatment of depression but the remaining task is to develop effective PA interventions applicable into routine care. The wider aim of our trial is to promote the implementation of PA interventions in inpatient treatment of depression.

Strengths of this research project include:

First, we measure PA objectively (with some constraints: some types of PA cannot be registered correctly or at all like climbing or swimming and wear time cannot be controlled) and subjectively and provide an assessment of depression severity by blinded raters as well as subjectively reported depressive symptomsSecond, the population is generalizable, for being recruited in a naturalistic clinic field in different study centers. Center effects can be analyzedThird, we will provide follow‐up dataFourth, a unique aspect of our PA intervention is that it is personalized and adaptive concerning intensity, length, frequency, and personal circumstances and that is developed based on an empirically supported psychological background. Patients can execute it and continue it afterward in self‐managementFifth, we take into account the effect of comorbid anxiety on our results

Our findings will contribute to the research field of exercise and depression in severely depressed patients and results will give opportunity for refining exercise‐related interventions in inpatient care.
